**Outcome variables:**

Cause of death registry and CVD diagnoses from hospitals (1994-2009): circulatory (ICD-10: I00-I99), coronary heart disease (ICD-10: I20-I25), stroke (ICD-10: I60-I69). Cardiovascular Disease in Norway (CVDNOR) is a register that contains all hospital discharge diagnoses (obtained from Norwegian hospitals, FS-data) for cardiovascular disease and diabetes, and also relevant procedures, such as surgery and cardiac interventions. CVDNOR covers the whole Norwegian population 1994-2009.

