## Research questions (RQ)

- (1) To investigate the risk and protective effects on CVD morbidity and mortality associated with various combinations of moderate alcohol consumption and binge drinking. We will here also look at risk in the sub-group of patients with pre-existing CVD.
- (2) To investigate if the effects of moderate alcohol consumption and binge drinking on CVD can be explained by or interact with mental distress (depression and/or anxiety).
- (3) To investigate if the effects of moderate alcohol consumption and binge drinking on CVD can be explained by or interact with cognitive ability (IQ), educational level, or other socioeconomic factors.
- (4) First, to investigate how alcohol consumption in family members are related to CVD risk among index individuals. Secondly, to use alcohol consumption among siblings and offspring as instrumental variable to assess the causal effects of alcohol consumption pattern on CVD.
- (5) Using pairs of siblings, monozygotic and dizygotic twins discordant for CVD to estimating the association between moderate alcohol and binge drinking and CVD within families. These results will adjust for early life and family factors.
- (6) To assess familial aggregation of mental distress, alcohol related mortality and CVD morbidity and mortality.

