### **Approaches, hypothesis and choice of method**

The study has some important strengths: the sample size and comprehensive data linkage, the availability of information on both moderate and binge drinking, reasonably long follow-up and linkage to information on both morbidity and mortality. Using morbidity data on hospital discharge on incidences of CVD increases the number of cases by a factor of approximately three to four compared to mortality data, and further increases statistical power further (RQ 1). This enables us to investigate combinations of moderate alcohol consumption and binge drinking. Having clinical endpoints in addition to mortality will be a significant improvement to the literature. It has been suggested that effects of binge drinking could be an artifact due to misclassification or have a non-atherosclerotic pathology.

The study will be able to look into more detail than has previously been possible on the long-term prognosis among patients with preexisting CVD or other high risk subgroups (RQ 1). In terms of drinking patterns, the results of individual level cohort studies mainly apply to cohorts who predominantly drink regularly with few heavy drinking occasions. Adequate power to investigate the combined effect of moderate and binge drinking requires large cohorts with enough data on the distribution of such drinking patterns within a population and information on exposure to other heart disease risk factors, pre-existing CVD as well as cognitive ability, mental distress and family data.

We will in this study be able to investigate if the abstainers might be a selected group more closely, and for a wider range of potential underlying factors, than has previously been done (RQ 2 and 3). An assessment on how these factors relate to alcohol consumption and heart disease will also broaden our understanding on the clinical and public health impact of alcohol in groups at particularly high risk (RQ1 and 2).

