### **Data sources**

The Cohort of Norway (CONOR) Data from 10 epidemiological studies (n=181,891) from 1994-2003 have been merged into a national database. All the surveys included self-reported health and selected diseases, various risk factors, socio-demographic factors, use of medications and physiological measures such as blood pressure, cholesterol, triglycerides, waist and hip circumference, height and weight.

The Norwegian Twin Registry (NTR) Panel II were born 1915-1960. Questionnaires on alcohol consumption were sent out in 1980 and 1990 and 14 500 responded to one of these. These questionnaires included detailed reports on health and risk factors.

Norwegian Family Based Life course Study Data from all 7,400 000 Norwegian citizens alive between 1960 to 2010 has been linked to family data and several health surveys and registers. Family linkage is available for more than 90 % of those born after 1940. This is linked to several other cardiovascular health surveys in addition to CONOR (in total 730,000) and the Conscript Registry.

Hospital discharges on cardiovascular diseases in Norway (FS-data): Data on all cardiovascular hospitalizations in Norway between 1994 and 2009 has been obtained through patient administrative systems at Norwegian hospitals. This includes coronary heart disease (both myocardial infarction and unstable angina), stroke and atrial fibrillation.

Social security registry (FD-trygd): Data on disability pension, sickness and social security benefits on all Norwegian citizens from 1992 onwards. Diagnosis will be ICD-10: F01-F99 (Mental, behavioral and neurodevelopmental disorders)

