### **Samples (sub-populations)**

#### **RQ 1:**

The CONOR and the NTR will be pooled together and the NTR will be used as a cohort for this purpose. This will include n=47,848 from CONOR and n=8028 individuals from NTR (n=55,876 in total) with complete data on both moderate and binge drinking. Mean year of birth is 1947 in CONOR and 1941 in the NTR sample. More deaths occur in the NTR (n=1453 deaths) compared to CONOR (n=1805 deaths). Number of CVD deaths in the CONOR sample with follow-up until 2010 is 547. Based on the proportion of CVD mortality and all-cause mortality and number of fatal and non-fatal cases in the FS-database, total

number of cases, including both CONOR and the NTR is expected to be 3000 IHD and 3500 cases of stroke.

RQs 2 and 3:

This will include the CONOR and twin populations linked to the FS-data on hospital discharges, the Cause of Death Registry, the Conscript Registry (cognitive ability) and Social Security Registry (mental health problems). Two separate sub-populations of CONOR will be studied: all subjects who responded to items on moderate alcohol consumption (n=162,048) and, nested in this sample, those who responded to items on both moderate and binge drinking (n=47,848). In the first group there are 3774 deaths from CVD. There are in total 9735 acute myocardial infarction and 8926 stroke incident cases from the FS-database in CONOR. For the second group, see RQ1.

RQ 4:

This issue will be analyzed in a linkage between CONOR, cardiovascular health surveys in the Norwegian Family Based Life course study and the FS-data on hospital discharges. There are 116,037 individuals in CONOR with information on parents and siblings. Of these, 109,800 individuals have responded on the moderate alcohol consumption question with 9729 CVD deaths in fathers and 31,050 on the binge drinking question with 1854 CVD deaths occurring after the year of CONOR examination.

RQ 5:

CONOR: There are 48,401 siblings in CONOR with the same mother and father. 1025 of these have by 2010 died (281 CVD). We expect approximately 1400 CVD endpoints in the FS-database. For the second group on siblings, see RQ 1.

RQ 6:

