Data analysis: For time to event outcomes such as morbidity and mortality the primary modelling strategy is to use Cox proportion hazard regression models. In RQ 1 the effect of moderate alcohol consumption will be analysed by adjusting for binge drinking and across strata of binge drinking (interaction term will be fitted to formally test if the effect differs). In RQ 2-3 the same strategy will be employed using strata of cognitive ability and mental health. In RQ 4 the aim is to see if using alcohol consumption among family members as instrumental variable will reproduce a protective effect of moderate alcohol consumption as seen in conventional analysis. Using instruments, it will also be possible to estimate the effect sizes and compare the effect and pattern in CONOR participants with that of their sibling. To achieve this, z-scores will be calculated based on units of alcohol consumption reported. For RQ 5, the effects of alcohol consumption will be estimated by comparison between siblings or co-twins ("fixed effect"). This approach effectively matches out all factors shared between siblings that may confound the effect of alcohol on cardiovascular mortality reported in studies of unrelated individuals. The analyses will be conducted in the statistical software STATA. Age, smoking status and number of cigarettes per day in smokers, physical activity, self-reported disease (CVD, diabetes, antihypertensive medication) and psychosocial distress at baseline will be adjusted for as potential confounders. In

familial aggregation analysis, we will estimate to what extent alcohol related mortality co-occur in first degree family members with CVD morbidity and mortality and mental distress by summing up number of family members with any of these traits.

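### In the pre-existing-CVD subgroup of RQ 1, the coronary and stroke code ranges let a discharge for the entry disease meet the endpoint

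*Protocol*

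**What the plan says.** Outcome variables takes endpoints from the death registry and from hospital diagnoses. The broadest is given as "Cause of death registry and CVD diagnoses from hospitals (1994-2009): circulatory (ICD-10: I00-I99", and the two specific ones as "coronary heart disease (ICD-10: I20-I25), stroke (ICD-10: I60-I69". The hospital register is described as holding "all hospital discharge diagnoses (obtained from Norwegian hospitals, FS-data) for cardiovascular disease and diabetes", along with relevant procedures.

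Research questions, RQ 1, adds a subgroup: "We will here also look at risk in the sub-group of patients with pre-existing CVD". The section on approaches and choice of method presents this as a strength, offering more detail on "long-term prognosis among patients with preexisting CVD or other high risk subgroups (RQ 1".

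Under Statistical methods, baseline disease is handled by covariate adjustment: "self-reported disease (CVD, diabetes, antihypertensive medication) and psychosocial distress at baseline will be adjusted for as potential confounders".

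Two other places describe the hospital data more narrowly. Data sources says "This includes coronary heart disease (both myocardial infarction and unstable angina), stroke and atrial fibrillation". The Samples section for RQs 2 and 3 says "There are in total 9735 acute myocardial infarction and 8926 stroke incident cases from the FS-database in CONOR".

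**The concern.** The two blocks mix codes for new acute events with codes for established or past disease. That matters little for a first coronary diagnosis in someone without known disease. It matters in a subgroup selected for having the disease. There, the stated endpoint overlaps the condition for entry, and a hospital record that restates the old infarction or the after-effects of the old stroke satisfies the definition as written.

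At stake is what the subgroup result means. The stated aim is long-term prognosis. If some endpoints only restate the entry disease, the alcohol hazard ratio becomes a mixture of the effect on new events and the association of drinking with being readmitted or recoded. A reader could not separate the two afterwards.

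**Working it through.** The protocol states no figure on this point to reproduce. It gives no subgroup size, no expected events for the subgroup, and no breakdown of codes within the blocks. The check is therefore a reading of the sections against each other, followed by an illustration with assumed shares.

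**1. What the blocks contain.** I20-I25 includes I25 (chronic ischaemic heart disease, including old infarction). I60-I69 includes I69 (sequelae of stroke). These meanings come from ICD-10, the classification the protocol adopts, not from its text.

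**2. Apply the definition to one participant.** A person enters the RQ 1 subgroup because of an infarction before baseline. A later discharge carries I25 for that known disease. I25 lies within I20-I25, so the definition is met. The same holds for a past stroke and I69.

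**3. Look for a rule that would prevent this.**
- Code exclusions: none in Outcome variables.
- Restriction to main diagnosis, acute admission or a gap from the index event: none. The source is described as all discharge diagnoses.
- Covariate adjustment: it acts on the exposure comparison and cannot reclassify an outcome. If the subgroup is defined by self-reported CVD, that covariate is constant within it.
- The word incident: it describes case counts in the Samples section and is not defined. It does not separate new from old disease in people who already have the disease.

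**4. Which definition do the case counts follow?**

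| Place in Samples section | Coronary term and count | Cerebral term and count |
|---|---|---|
| RQ 1, CONOR plus NTR | IHD, 3000 | stroke, 3500 |
| RQs 2 and 3, CONOR | acute myocardial infarction, 9735 | stroke, 8926 |
| NTR, 1980 questionnaire | IHD, 1700 | cerebrovascular disease, 1950 |
| NTR, 1990 questionnaire | IHD, 900 | cerebrovascular disease, 1040 |

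The IHD and cerebrovascular terms fit the blocks. Acute infarction does not cover the whole of I20-I25. The stroke counts could follow either definition.

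**5. Illustration of size.** Let f be the share of counted endpoints in the reference group that are re-recordings of the entry disease. Let HR be the hazard ratio for new events and r the hazard ratio for re-recordings. Then

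observed HR = HR × (1 − f) + r × f.

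The protocol gives neither f nor r. Take r = 1 (re-recording unrelated to drinking), and the relative risks 1.45 (binge drinking) and 0.75 (average consumption) from Statistical methods:

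| f (assumed) | from 1.45 | from 0.75 |
|---|---|---|
| 20% | 1.45 × 0.8 + 0.2 = 1.36 | 0.75 × 0.8 + 0.2 = 0.80 |
| 40% | 1.45 × 0.6 + 0.4 = 1.27 | 0.75 × 0.6 + 0.4 = 0.85 |
| 60% | 1.45 × 0.4 + 0.6 = 1.18 | 0.75 × 0.4 + 0.6 = 0.90 |

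The observed value is a weighted average of HR and r, so the direction depends on r. The protocol itself raises the problem of sick quitters. If people with old disease have stopped drinking and are also readmitted more, then r for moderate drinkers against abstainers is below 1. If r fell below 0.75, the observed ratio would move further from 1, not toward it.

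**The case against.** The strongest reply is that no section says readmissions count as new events. Rules on first events, main diagnosis and washout commonly sit in a statistical analysis plan, which is not shown here. The protocol's language of incident cases and of developing CVD during follow-up points to new disease. Data sources describes a source and does not define an endpoint. The RQ 1 counts are for IHD, which agrees with the block. For a question about prognosis, admission for progressing ischaemic disease can be a legitimate outcome. The added cases from morbidity data are also a stated strength that a narrow code list would erode.

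Much of this stands, and it rules out several stronger readings that a reader might infer:
- That the protocol counts readmissions as new events. It does not say so. What follows from the text is that such a discharge can meet the definition.
- That the subgroup endpoint mostly measures health-care contact. The share of such codes is not given.
- That event dates in the full cohort are follow-up visits. The source is described as hospitalisations and discharge diagnoses; visits are not mentioned.
- That the bias runs toward 1. This holds only if re-recording is unrelated to drinking.
- That every non-fatal endpoint should become acute main diagnoses only. In the full cohort this trades specificity against event numbers, and the incident wording supports the planned blocks for first events.

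The reply does not dispose of the subgroup problem. The code ranges are not a detail left for later: the protocol fixes them, and applied as fixed they overlap the entry condition of a subgroup that the protocol also plans.

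**Conclusion.** The point holds for the pre-existing-CVD subgroup of RQ 1. As defined, a discharge after baseline carrying I25 or I69 for the disease that defined entry can count as an endpoint, and adjustment for self-reported CVD does not stop it. Neither the size nor the direction of the resulting bias can be determined from the protocol. The diluted ratios above are illustration only. They rest on assumed shares, on re-recording being unrelated to drinking, and on relative risks quoted for a cohort-level power calculation, not for this subgroup.

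In the full cohort the point is narrower. An I69 code can only follow a stroke that has already happened, so it should not date a new non-fatal stroke. I25 can be a first diagnosis in someone without known disease, so keeping it there is defensible. The expected case counts use different disease terms and need labelling, but they do not show that the RQ 1 count is wrong.

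**What to change.** - **Pre-existing-CVD subgroup.** Count as hospital endpoints only new acute events after baseline, for example I20.0, I21-I22, I60, I61, I63 and I64, plus CVD death. Do not count I25 or I69 discharges.
- **Full cohort.** Keep the planned blocks for first events, but exclude I69 from the non-fatal stroke endpoint. Report the acute-code definition as a sensitivity analysis.
- **Case counts.** In the Samples section, state which definition each expected count follows: acute infarction or IHD, stroke or cerebrovascular disease.

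This needs a change of protocol wording and a code list applied to the hospital data already obtained. It is best settled before the alcohol results are seen. The price is fewer non-fatal events in the subgroup. The protocol gives no figure from which to estimate the loss, so the number of events under each definition should be tabulated, without regard to exposure, when the list is fixed.

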## **Statistical methods**

Sample size and power: The materials used to address RQ 1 is considerably higher powered than those used in previous research. Power calculations have been conducted using the `sampsi` command in STATA and the program `Quanto` for interaction terms. RQ 1: Two options have been used: Either to report the effect of moderate alcohol consumption adjusted for binge drinking or to test formally for interaction between average alcohol consumption and reported binge drinking. We have calculated the last because we consider this the most conservative approach. The relative risk of main effects has for average alcohol consumption reported to be 0.75 and for binge drinking 1.45. If we assume that 10 % in the cohort develop CVD in the follow up period, power of 80 % and set p-value at 5 % for two sided tests, we would need a sample of 7,960 individuals, which is well below our sample of 55,876 individuals. RQ 2 and 3: Prevalence of mental distress in CONOR is on average 10 %, and the effect of depression on CVD is assumed to be 1.6. If we want to detect a 50 % difference in effect of binge between depressed and not depressed subjects, we would need 26,740 individuals (in our sample  $n=47,848$ ), and for frequency of alcohol use 53,680 individuals (in our sample  $n=162,048$ ). RQ 4: As we do not know the strength of association between alcohol consumption and sibling and parental CVD morbidity and mortality, it is difficult to calculate sample size exactly for this sub study. For this reason, we have preliminary investigated this issue, and found that it appears to be higher risk of CVD in fathers and same sexed sibling among those who are abstainers compared to those who drink moderately. The hazard ratio of CVD death in fathers among those who abstain from alcohol compared to moderate drinkers was 0.93 (0.88-0.99). RQ 5: It is not straightforward to estimate power in within sibling analyses. With a total of 5050 CVD endpoints, and based on our experiences in an analysis with similar design and number of endpoints, we consider it likely that we will be able to detect differences large enough to be theoretically interesting. RQ 6: With 3500 alcohol related cases, we consider it highly likely that we will be able to detect meaningful degree of familial aggregation for mental distress and CVD morbidity and mortality.

Data analysis: For time to event outcomes such as morbidity and mortality the primary modelling strategy is to use Cox proportion hazard regression models. In RQ 1 the effect of moderate alcohol consumption will be analysed by adjusting for binge drinking and across strata of binge drinking (interaction term will be fitted to formally test if the effect differs). In RQ 2-3 the same strategy will be employed using strata of cognitive ability and mental health. In RQ 4 the aim is to see if using alcohol consumption among family members as instrumental variable will reproduce a protective effect of moderate alcohol consumption as seen in conventional analysis. Using instruments, it will also be possible to estimate the effect sizes and compare the effect and pattern in CONOR participants with that of their sibling. To achieve this, z-scores will be calculated based on units of alcohol consumption reported. For RQ 5, the effects of alcohol consumption will be estimated by comparison between siblings or co-twins ("fixed effect"). This approach effectively matches out all factors shared between siblings that may confound the effect of alcohol on cardiovascular mortality reported in studies of unrelated individuals. The analyses will be conducted in the statistical software STATA. Age, smoking status and number of cigarettes per day in smokers, physical activity, self-reported disease (CVD, diabetes, antihypertensive medication) and psychosocial distress at baseline will be adjusted for as potential confounders. In

familial aggregation analysis, we will estimate to what extent alcohol related mortality co-occur in first degree family members with CVD morbidity and mortality and mental distress by summing up number of family members with any of these traits.

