## **2. Aspects relating to the research project**

### **Background and status of knowledge**

Alcohol has a negative effect on many health-related outcomes but for heart diseases the effects seem to be mixed. Alcohol use is negatively related to hypertensive disease, hemorrhagic stroke and atrial fibrillation. For ischemic heart disease (IHD) and ischemic stroke (cardiovascular diseases, CVD), the relationship is complex. Chronic heavy alcohol use has been associated with adverse cardiovascular outcomes. But light to moderate drinking seems to be related to reduced risk of ischemic diseases.

It is not well understood to what extent frequent episodes of heavy alcohol consumption may counteract the beneficial effect on heart disease and by which mechanisms episodes of heavy alcohol have a negative effect on heart disease. Even rare and occasional episodes of binge drinking seem to increase the risk in a recent study from the northernmost part of Norway. One would expect the protective effect to be more pronounced in individuals who do not binge drink, and not present in individuals who report substantial binge drinking. A recent meta-analysis on binge drinking including only 4718 IHD events gave some support for this notion. Our study will add to this by 6500 CVD cases.

Norwegian studies on adolescent and adult abstainers have shown higher risk of psychosocial factors and might suggest a J-shaped pattern. A general finding is that abstainers tend to have worse health and are poorer. One interpretation of this and similar findings is that since alcohol is such an important token in social interaction, abstainers are likely to differ as a social group and have a wide range of individual characteristics that could put them at increased risk of several health problems. Those who have moderate intake have in studies been shown to have higher cognitive ability compared to abstainers and that heavy drinkers have lower cognitive ability.

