**Main variables (see full description at [FHI webpage](#))**

**Moderate alcohol consumption**

Questions in CONOR:

1) “Approximately, how often have you during the last year consumed alcohol?” Eight response alternatives were recoded into five categories: Never/seldom, once per month, 2-3 per month, about once a week, 2-3 times a week, 4-7 times a week. 2) “When you drink, how many glasses do you usually drink?” 3) “When you drink, do you usually drink beer, wine or liquor?”

Questions in NTR:

1) “Do you drink beer?” 2) “Do you drink wine?” 3) “Do you drink liquor?” For each of these three questions, quantity was assessed by: “Do you drink less than a glass each day, 1-2 glasses each day or more than 2 glasses each day”.

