**Binge drinking**

Questions in CONOR:

“Approximately how often during the past 12 months have you consumed alcohol corresponding to at least 5 glasses of liquor in 24 hours?”

In all 47,848 participants (26,151 men and 21,697 women), and answers varied from zero to 99 times during the last year. Nearly half (46.3%) reported zero, and the frequency was a higher in men than in women.

In NTR:

1990 questionnaire: “Approximately how many times during one year do you drink more than 5 bottles of beer, one bottle of red or white wine or a quarter bottle of liquor?” (Never, 1-4 times a year, 5-10 times a year, once a month, 2-3 times a month, once a week, 2-4 times a week or every day or almost every day?)

Life course socioeconomic position: Highest educational level, household income (yearly updated), Childhood parental occupational class and education, and housing conditions from Censuses 1960 onwards).

Cognitive ability/Intelligence in late adolescence: The Norwegian National Conscript Service examines more than 90% of the male population at age 18-19 years. General ability is a composite score based on 3 speeded subtests. The Arithmetic Test (25 minutes) has 30 items in prose and measures logical reasoning and arithmetic and algebraic ability; it is similar to the arithmetic test in the Wechsler Adult Intelligence Scale (WAIS). The Word Similarities Test (8 minutes) is a multiple-choice test with 54 items, akin to the vocabulary test in WAIS. The Figures Test (20 minutes) has 36 multiple-choice items with 6 or 8 alternatives and is similar to Raven’s Progressive Matrices.

The CONOR mental health index: This consists of summative index including seven questions on mental distress scored 1-4: “Have you, in the course of the last two weeks, felt: Nervous and unsettled? Troubled by anxiety? Secure and calm? Irritable? Happy and optimistic? Sad/depressed? Lonely?” Response categories are “No”, “A little”, “Quite a bit” and “Very”. This index captures a combination of symptoms of anxiety and depression. This index has been validated, has good internal consistency and correlates highly with the total score for Hospital Anxiety and Depression Scale (HADS) ( $r=0.76$ ) and with Hopkins symptom checklist (HSCL-10) ( $r=0.70$ ).

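### The pooled never/seldom category changes composition across binge strata, so the RQ 1 interaction test can show stronger protection in non-bingers without effect modification among drinkers

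*Protocol*

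**What the plan says.** The Data analysis paragraph of the protocol's Statistical methods section sets a Cox model for RQ 1. The effect of moderate drinking is estimated with adjustment for binge drinking, and also "across strata of binge drinking (interaction term will be fitted to formally test if the effect differs"). No reference category is named, and the test is not limited to drinkers.

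The CONOR exposure is defined under Moderate alcohol consumption. The item asks "how often have you during the last year consumed alcohol", and the coding is: "Eight response alternatives were recoded into five categories: Never/seldom, once per month, 2-3 per month, about once a week", followed by two higher levels. The text announces five categories and lists six.

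The CONOR binge item asks "Approximately how often during the past 12 months have you consumed alcohol corresponding to at least 5 glasses of liquor in 24 hours". On the answers, the protocol reports: "Nearly half (46.3%) reported zero".

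On expectations, Background and status of knowledge says: "One would expect the protective effect to be more pronounced in individuals who do not binge drink". It also describes abstainers as less healthy and poorer. Approaches, hypothesis and choice of method describes a J-shape in which abstainers, as the lowest group, have higher CVD risk than moderate drinkers, possibly through reverse causality and sick quitters. It also promises: "We will in this study be able to investigate if the abstainers might be a selected group more closely".

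**The concern.** A person who drank nothing in the last year cannot have had a binge in that year. The pooled lowest category therefore holds different people in different binge strata, and a contrast against it does not mean the same thing in each.

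If abstainers carry excess risk, moderate drinking looks more protective among non-bingers simply because their comparison group contains abstainers. That is the direction the protocol predicts. The interaction is RQ 1's formal test and the one for which the protocol calculates power. A positive result could not then be told apart from abstainer selection, which is the rival explanation the project wants to examine. The family instrument proposed against sick quitters belongs to another research question and does not protect this test.

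**Working it through.** **1. The protocol's own figure.** Sample size and power gives 7,960 people for the RQ 1 interaction test, against 55,876 available. This can be neither reproduced nor refuted, because the exposure prevalences and the interaction effect are not stated. With binge prevalence 10-53.7% and moderate-drinking prevalence 20-70%, 7,960 corresponds to an interaction ratio of about 1.46 to 2.04. The available sample is 55,876 / 7,960 = 7.0 times larger, so the test will also respond to much smaller ratios, including artefactual ones.

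**2. Size of the artefact.** Let a be the abstainer share of the never/seldom group at zero binge, and h the hazard ratio of abstainers to seldom drinkers. With no interaction among drinkers, the spurious ratio of hazard ratios is

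R = (1 - a) + a × h.

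If h = 1, then R = 1 and there is no bias.

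The documents give neither a nor h. Assume abstainers to moderate drinkers = 1/0.75 = 1.333 (the protocol's 0.75 is for average consumption, so this use is an assumption) and seldom to moderate drinkers = 1.05. Then h = 1.333/1.05 = 1.27, and

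- a = 0.3: R = 0.7 + 0.3 × 1.27 = 1.08
- a = 0.5: R = 0.5 + 0.5 × 1.27 = 1.135
- a = 0.7: R = 0.3 + 0.7 × 1.27 = 1.19

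**3. Rejection probability.** The variance of log R is the sum of 1/events over four cells (never/seldom or more frequent drinking, by zero or any binge). Inputs:

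- Any binge: 53.7% (100 - 46.3, CONOR).
- Binge relative risk: 1.45 (Sample size and power).
- Events: 10% of 55,876 = 5,588. A lower case scales the 547 CVD deaths in the CONOR binge sample by CONOR's ratio of hospital cases to CVD deaths: 547 × (9,735 + 8,926)/3,774 = 2,705.
- Assumed: never/seldom is 40% of non-bingers and 2-10% of bingers; moderate-to-seldom hazard ratio 0.90.

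Example with 5% of bingers in never/seldom, R = 1.135 and 5,588 events. Cell shares are 0.1852, 0.2778, 0.0269 and 0.5102; relative hazards are 1.135, 0.90, 1.45 and 1.305. Events are then about 1,008, 1,199, 187 and 3,194. SE = √(1/1,008 + 1/1,199 + 1/187 + 1/3,194) = 0.087; ln 1.135 / SE = 1.46; rejection probability = 31%.

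| Never/seldom among bingers | 5,588 events: R = 1.08 / 1.135 / 1.19 | 2,705 events: R = 1.08 / 1.135 / 1.19 |
|---|---|---|
| 2% | 10% / 17% / 28% | 7% / 11% / 16% |
| 5% | 15% / 31% / 51% | 10% / 17% / 28% |
| 10% | 20% / 44% / 70% | 12% / 24% / 41% |

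At a = 0.25 and h = 1.15, R is 1.04 and rejection with 5,588 events is only 6-8%.

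**4. Check by simulation** (4,000 runs per setting; a = 0.5, 5% of bingers in never/seldom, N = 55,876, 10% events). With the pooled group as comparator, rejection was 4.9% at h = 1.00, 12.7% at 1.15, 43.3% at 1.33 and 74.3% at 1.50. With abstainers removed it was 4.7-5.4% throughout.

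**5. Does naming another reference cure it?** Not by itself. A joint test of all category-by-binge terms does not depend on the reference level. With six categories and the settings of step 4, the five-degree-of-freedom test rejects about 23% of the time at h = 1.33 and 47% at h = 1.50, whichever level is the reference.

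**The case against.** The strongest reply is that the protocol never makes never/seldom the RQ 1 reference. A reader might infer this from the coding and the J-shape discussion, but it is not stated. The power text speaks of average consumption, CONOR also asks glasses per occasion, and an analysis plan could set a different reference or a quantity-based exposure. This stands as a limit on the wording. It does not remove the point: the pooled category and the unrestricted interaction test are both in the protocol, and step 5 shows that a new reference alone is not enough if the pooled level stays in the test.

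The bias also needs abstainers to differ from seldom drinkers. The protocol describes excess risk only against moderate drinkers, and the planned adjustment for smoking, physical activity, reported disease and distress may remove part of it. The one abstainer figure, a hazard ratio of 0.93 for fathers' CVD death, contradicts its own sentence, so the numbers do not settle the direction. All of this stands.

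Two stronger readings are tempting. One is that the test would falsely reject 26-84% of the time. That range needs about half of each binge stratum in the lowest category, which conflicts with the premise that few never/seldom drinkers binge. The other is that the recode removes abstainers from the study. The eight raw CONOR responses exist, the RQ 4 power text already reports an abstainer contrast, and NTR asks about each beverage separately.

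Finally, RQ 1 is framed as combinations of moderate and binge drinking, so a joint exposure is in the spirit of the plan. The test as described still does not separate abstainers.

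**Conclusion.** The point holds in a limited form. With never and seldom pooled and no restriction to drinkers, the lowest category changes composition between the zero-binge stratum and the others. The RQ 1 interaction test can then reject without effect modification among drinkers. If abstainers have the higher risk, the artefact runs in the hypothesised direction; if the two groups have equal risk, the test is valid.

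The size is conditional. Rejection of about 10-70% (5,588 events) or 7-41% (2,705 events) rests on assumed shares and on spurious ratios of 1.08-1.19, none of which the documents give. It is close to 5% for a small abstainer excess.

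The pooled category concerns CONOR, 47,848 of the 55,876 in the RQ 1 sample (86%). NTR uses per-beverage items ("Do you drink less than a glass each day, 1-2 glasses each day or more than 2 glasses each day"), but its abstainers cannot report binges either. The mismatch between five announced and six listed categories is a plain error that needs no assumption.

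**What to change.** - Return to the eight original CONOR responses and separate never from seldom as far as they allow; keep NTR abstainers separate in the same way.
- Name one common reference group for RQ 1: non-bingeing drinkers at a stated frequency.
- Make the formal moderate-by-binge interaction test among current drinkers only, and report abstainers as a separate contrast against the same reference.
- Correct the number of categories to match the list.

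The cost is a recode of existing responses and one changed model statement. The interaction test loses the abstainers' events, so it is somewhat less precise, and it answers a narrower question: effect modification among people who drink.
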